#### Effectiveness trial

The effectiveness trial will be run in Victoria for practical reasons (ie, funding constraints regarding in-school data collection and professional learning sessions, and multiple ethics approvals that would be required from Departments of Education in different states/territories). Up to six Victorian special schools (up to n=3 intervention and n=3 waitlist control; out of n=61 eligible schools) will be recruited for the effectiveness trial. School staff in the intervention school will be offered at least one in-person professional development opportunity at their school. School staff will also access the *TransformUs All Abilities* training material, programme components and programme resources through the *TransformUs* website (https://transformus.com.au) and will be encouraged to use the strategies in their classrooms/school.

Intervention effectiveness will be assessed in relation to device-measured students’ physical activity and sedentary time (primary outcomes), sleep, physical literacy and cognitive functions (secondary outcomes), as well as teachers’ confidence and competence in implementing the *Transform All Abilities* programme (secondary outcomes). Teachers’ feedback on their experience of delivering the programme and the perceived barriers and facilitators to implementation will be sought with audio-recorded interviews/focus groups at the end of the trial. Additionally, at the end of the trial, we will conduct a 45 min focus group session with a small group of students at each intervention school to understand how students with disabilities view the opportunities for physical activity throughout the school day. With these discussions, we will aim to understand (1) students’ perceptions of the *TransformUs All Abilities* programme; (2) their enjoyment in relation to the programme and (3) perceived barriers and facilitators to the implementation of physical activity strategies in their schools.

The principal/nominated school leader will help to oversee the implementation of the intervention in the school. A nominated school contact/liaison will distribute information on the study for the purposes of recruiting staff and students for the evaluation and will help to coordinate the assessments when the research team visits the school.

### Recruitment strategy

#### Implementation trial

Eligible school staff (see eligibility criteria table 1) who indicate willingness to participate in the trial at registration on the *TransformUs* website will be invited to click on a hyperlink connecting them to an online plain language description of the study, a consent form and a baseline survey.

**Table 1 T1:** Inclusion and exclusion criteria for each trial

Target	Inclusion criteria	Exclusion criteria
Implementation trial		
School staff	Teachers, specialist support staff and other staff directly involved in teaching and learning activities, working in Australian government or independent schools located in Victoria (mainstream/special primary/secondary), Queensland or South Australia (special primary/secondary; mainstream secondary), who register for the *TransformUs* programme via the website.	Teachers, specialist support staff and other staff working at any Catholic school across Australia Teachers and other staff working at government or independent schools in New South Wales, Western Australia, Tasmania, Northern Territory and Australian Capital Territory will be able to register for the *TransformUs* programme but will not be invited to participate in the implementation trial. Other staff not directly involved in teaching and learning activities (eg, school administrative staff)
Effectiveness trial		
Schools	Up to six special government or independent special schools (primary, secondary or combined) located in Victoria catering for students with mild to moderate intellectual disability.	Mainstream schools Catholic schools Schools located in New South Wales, Western Australia, Tasmania, Northern Territory, Australian Capital Territory, Queensland, South Australia or outside Australia
School staff	School leaders: 1 nominated school leader per school (n=6) Teachers and teacher aides delivering the programme (approx. n=20)	School staff from schools not recruited for the trial
Students	Around 125 students with disabilities, both males and females, aged 6–18 years, attending one of the recruited schools. Focus groups (subsample): 18–30 students in total (max n=6 students per group)	Students younger than 6 years or older than 18 years.

#### Effectiveness trial

Principals or nominated school leaders will receive an invitation for their school to participate in the effectiveness trial. After receiving informed principal consent, schools will distribute recruitment information to parents/children. Parental written/electronic consent for their child to participate in the study will be sought prior to the study commencement. In addition to the informed consent received from parents/guardians, verbal assent from students will be obtained prior to any student assessment through any communication means (eg, verbally or via alternative and augmentative communication). Allocation to intervention/wait-list control will be done pragmatically, based on schools’ preference.

### Inclusion/exclusion criteria

The eligibility criteria for each study are outlined in table 1.

### Measures

An overview of the outcomes for the implementation-effectiveness trial is presented in table 2. More detailed information on each trial is available in the following sections.

**Table 2 T2:** RE-AIM evaluation of the *TransformUs All Abilities* implementation and effectiveness trial

RE-AIM dimension	Measure/construct	Data source
Reach	Number and characteristics of registrants on the *TransformUs* website who indicate having children with disability in their classroom Estimated number of teachers and schools exposed to *TransformUs All Abilities* Relative representativeness of schools and students potentially exposed to *TransformUs All Abilities* (based on publicly available data on school characteristics and enrolments)	Web analytics (*TransformUs* website) Registration survey (*TransformUs* website) *MySchool* website (www.myschool.edu.au)
Effectiveness	Students Physical activity and sedentary behaviour (primary outcome) Sleep Physical literacy Cognitive functions (working memory) Students’ views on *TransformUs All Abilities*	Students Wrist-worn accelerometers (ActiGraph) Physical Literacy in Children Questionnaire (PL-C Quest—on iPad) Corsi Block-Tapping task (on iPad) Focus group discussions Teachers Teacher survey (pretrial and post-trial) Teacher interviews post-trial
Adoption	Reason for uptake of the programme Organisational readiness Organisational climate	Web analytics (*TransformUs* website) Registration survey (*TransformUs* website) Teacher survey (pretrial and post-trial) Teacher interviews post-trial
Implementation	Teaching practices and intention to implement Confidence, competence and barriers to implementing *TransformUs All Abilities* Teachers’ perceived barriers and facilitators to implementing *TransformUs All Abilities* Resources accessed (type, frequency) Strategies implemented by teachers (types, frequency)	Teacher survey (pretrial and post-trial) Teacher interviews post-trial Ecological Momentary Assessment (EMA) Web analytics (*TransformUs* website)
Maintenance	Teacher perception of potential to become part of routine educational practices Teacher views on factors affecting the long-term sustainability	Teacher survey (pretrial and post-trial) Teacher interviews post-trial

#### Implementation trial

School staff’s demographic information, decision to register to the *TransformUs* website, their current teaching practices, organisational readiness, organisational climate, intention to implement the *TransformUs All Abilities* strategies will be collected at baseline using an online survey. Most constructs in the survey are measured using several items anchored to a 5-point Likert scale (strongly disagree—strongly agree). The online survey will be administered again 6 months after the registration to assess changes in school staff’s perceptions regarding *TransformUs All Abilities*. To assess frequency of intervention delivery, responses to up to three EMA text messages per school term will be sought for up to six school terms in total. Teachers will be asked to select from a list of seven strategies they used in the last week (figure 2).

**Figure 2 F2:**
[figure not shown]
Ecological Momentary Assessment text messages used in the *TransformUs All Abilities* trial.

To gather additional information on school staff’s experience with *TransformUs All Abilities*, a subsample of participants will be invited to participate in an interview at the end of 6 months. Interview questions will relate to participants’ experiences of delivering the programme, including any barriers or enablers. Throughout the trial, we will regularly download data that will indicate the number of All Abilities registrations to the *TransformUs* website. Website usage data, such as accessing All Abilities online resources, will be captured via Google Analytics.

### Effectiveness trial

#### Student outcomes

##### Baseline and post-trial

At baseline and at the end of the trial (approx. 20 weeks), students will complete assessments at the school in the presence of a school staff member to ensure that they feel comfortable in the environment and with people they are already familiar with.

Physical activity, sedentary behaviour (primary outcomes) and sleep (secondary outcome) will be measured using tri-axial GT9X ActiGraph accelerometers (ActiGraph, Pensacola, FL, SA). Students will be asked to wear them on their non-dominant wrist for eight consecutive days, including sleep and excluding water-based activities (eg, swimming or bathing) at both measurement points. The ActiGraph GT9X has demonstrated validity and reliability in children and adolescents.^59^ Data will be processed in R (https://transformus.com.au/) using the GGRI package, to determine time spent sedentary, in MVPA, and light, moderate and vigorous physical activity during school, recess, lunch and across weekdays and weekends. Sleep duration will also be analysed. A similar approach has been used in children with disability.^60^

Physical literacy (secondary outcome) will be assessed using the pictorial Physical literacy in Children Questionnaire (PL-C Quest).^61^ The Australian Physical Literacy Framework describes physical literacy as ‘lifelong holistic learning acquired and applied in movement and physical contexts’, which comprises 30 elements within four domains (physical, psychological, cognitive and social).^62^ The PL-C Quest is the only pictorial survey aligned with the Australian Physical Literacy Framework that uses images to depict each of the 30 elements. Each question contains two pictures with an orange bunny cartoon performing some activities. Children are asked to pick the picture where they think the cartoon character is being the most like them if they were in that situation. Once they pick that picture, they are asked how much the picture represents them (a bit or a lot). The scale has good internal consistency and evidence of construct validity in over 600 Australian children.^63^ In 2021, this scale was used in a dissertation with Canadian participants with intellectual and developmental disabilities; feedback from those participants and parents/guardians was very positive as to ease of use and enjoyment.^64^ An interactive version of the PL-C Quest will be administered using iPads. It takes approximately 4 min for children without disabilities to complete this assessment. It may require up to 8 min for children with disabilities to complete it, depending on their level of functioning. A researcher will help students to complete the survey, as required.

Cognitive functions will be measured using a forward Corsi Block-Tapping task (forward) powered by Inquisit Web (Milliseconds Software, LLC). Many versions of this task have been developed based on the original paradigm developed by Corsi.^65^ The version used in this study is an adapted version of the task developed by Kessels *et al.*^66^ The task presents a sequence of boxes lighting up in yellow in a predetermined (pseudo-random) order. After the last block is lit up, the participant is required to tap on the boxes that appeared in yellow, following the order in which they were lit. The task starts with a sequence of two blocks (level 2) and can continue up to nine blocks (level 9). Each level offers two chances to correctly reproduce the sequence of blocks. The test ends if a participant fails to reproduce two sequences of the same length. The assessment will be delivered via the Inquisit app on an iPad. Participants are provided with a practice session before starting the task. The approximate completion time is 2–4 min.

##### Post-trial only

To understand how students with disabilities perceived the intervention strategies, we will conduct a minimum of three 45 min focus group discussions with students (around n=6 students per group: 18–30 students in total). Trained researchers will guide the discussion which will be around students’ perceptions regarding the physical activity strategies implemented in the trial (enjoyment, physical/mental effort, favourite activities, perceived barriers, suggestions for improvements, etc). Similar discussions will also be held with students in the wait-list control schools to learn more about students’ current experiences at schools in relation to movement-based activities, their preferences and potential interest in the types of activities included in the *TransformUs All Abilities* programme. All discussions will be audio recorded and later transcribed verbatim for analysis. Drawings or notes produced during the focus groups will be collected or photographed.

### School staff outcomes

School staff will complete the same survey described in the implementation trial section at baseline and 6 months later. Teacher responses to EMA text messages sent up to three times per term for the duration of the trial to the three intervention schools will be collected as a measure of fidelity. Teachers from the three intervention schools will be invited to participate in an interview at post- aimed at learning more about their experience with the programme.

### Sample size and power calculation

#### Implementation trial

Based on reach, we aim for at least 52 special schools (ie, 25% of the 208 eligible special schools) and 98 mainstream schools (ie, 5% of the eligible 1965 mainstream primary/secondary/combined schools) to uptake the *TransformUs All Abilities* programme.

#### Effectiveness trial

For our primary outcome—ActiGraph-measured MVPA (min/day)—we are aiming to recruit a total of 134 students (intervention n=67; control n=67). Allowing for a 30% drop-out and incomplete data (accelerometer not worn for enough hours per day or days over the week), this would still give us a sufficient power to detect statistically significant differences in the primary outcome.

For data to be analysed with linear mixed models (additional details available in section ‘Data Analysis’), the fixed effects were estimated with an a priori power calculation using G*Power software. Assuming a moderate effect size (f² = 0.15), an α error probability=0.05, and power (1 – β error probability) = 0.80, and the group variable as predictor, fixed effects were estimated to require 55 observations. To account for the random effects of clustering (students in the same classroom), a design effect of 1.82 was estimated (based on a coefficient of variation of 0.15 and an average number of five students per classroom and a conservative Intraclass Correlation Coefficient value of 0.20), suggesting that 100 observations would be required (ie, 55×1.82 = 100). Accounting for 25% attrition, the final total sample size needed for the effectiveness trial is 134 participants (ie, 100 ÷ (1–0.25) = 134), from 27 classrooms (134 ÷ five students per class=27).

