**Methods and analysis:**

This study employs a hybrid type II implementation-effectiveness trial to evaluate the *TransformUs All Abilities* programme, targeting all government and independent, primary and secondary schools in Victoria, as well as special and mainstream secondary schools in Queensland and South Australia (n=2173 eligible schools). The effectiveness trial will focus on a subgroup of government/independent special schools for students with mild to moderate intellectual disability in Victoria, involving up to three intervention and three waitlist control schools (n=61 eligible schools). In both trials, outcomes will be guided by the RE-AIM framework focusing on reach, adoption and implementation (implementation trial) and effectiveness (effectiveness trial), with data collected at baseline and 6 months. The effectiveness trial will focus on students’ device-measured physical activity and sedentary behaviour—primary outcomes—and sleep, physical literacy and cognitive functions—secondary outcomes. Teacher feedback on the programme’s adaptation and their experience with programme implementation will also be collected, alongside qualitative feedback from a subsample of students regarding engagement/enjoyment and suggestions for improvements. Implementation data will be analysed descriptively and using linear mixed models to test changes over time. Effectiveness outcomes will be analysed using linear mixed models to compare intervention and waitlist control, accounting for confounding and school/classroom clustering. Interview data will be thematically analysed.

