### Data analysis

Qualitative information collected from the interviews and focus groups will be analysed using thematic analysis^67^ in NVivo V.14 (released in 2023, Lumivero). Using a hybrid inductive/deductive approach,^68 69^ we will code data inductively and categorise codes in themes according to common implementation outcomes (ie, acceptability, adoption, feasibility, fidelity, penetration, sustainability and satisfaction).^57^ Where coded quotes do not apply to any of the preconcerted themes, new themes will be created.

Quantitative data will be analysed using Stata V.18 (Stata Corp. LLP). Preliminary analysis will be conducted to describe the sample (demographic characteristics and distribution of the scores on the outcomes of interest). Teacher-level outcomes from survey and EMA text message responses—including current teaching practices, organisational readiness/climate, teacher’s competence/confidence, and perceived barriers and facilitators in implementation, as well as frequency and types of *TransformUs All Abilities* strategies implemented by teachers (ie, EMA responses)—will be summarised descriptively. Changes over time in those outcomes’ scores will be analysed using linear mixed models. For teachers in the implementation trial, we will use time as a predictor variable (baseline/follow-up for survey scores; multiple time points for EMA). For teachers participating in the effectiveness trial, the predictor of interest will be the interaction between study group (intervention/control) and time. All models will be adjusted for common confounders (ie, teacher’s age, sex, years of teaching experience) and controlled for the random effect of classroom as a clustering variable.

Student-level primary and secondary effectiveness outcomes will be analysed using separate linear mixed models to assess the fixed effects of the intervention (ie, study group [intervention/control] × time [baseline/follow-up]) on each continuous outcome (ie, physical activity, sedentary time, sleep, physical literacy and cognitive functions), adjusting for common confounders (ie, age, sex and student disability/functioning) and controlling for the random effects of clustering (ie, students in classrooms). The effects of an interaction term between study group, time and student disability/functioning will also be explored, to see whether different levels of support moderate the intervention effects.

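### The trial is sized for one primary outcome (MVPA, min/day), but other sections make both physical activity and sedentary time primary, with no rule for two

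*Protocol article*

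**What the plan says.** The article describes the primary outcome of the effectiveness trial in two ways.

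- **One outcome.** Sample size and power calculation, Effectiveness trial: the primary outcome, in the singular, is "ActiGraph-measured MVPA (min/day"), with a target of 134 students. The same section gives f² = 0.15, alpha 0.05, power 0.80 and group as the predictor.
- **Two outcomes.** Abstract, Methods and analysis: "device-measured physical activity and sedentary behaviour—primary outcomes". Procedures and participants, Effectiveness trial: "device-measured students’ physical activity and sedentary time (primary outcomes"). Student outcomes, Baseline and post-trial: "Physical activity, sedentary behaviour (primary outcomes) and sleep (secondary outcome) will be measured". Table 2 also pairs physical activity with sedentary behaviour under a primary label, there in the singular.

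The Data analysis section states: "Student-level primary and secondary effectiveness outcomes will be analysed using separate linear mixed models". Its list of continuous outcomes has physical activity and sedentary time as separate entries. It does not mention MVPA in min/day, and it gives no hierarchy, co-primary rule or division of alpha.

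The student measures section also derives MVPA and sedentary time, together with "light, moderate and vigorous physical activity during school, recess, lunch and across weekdays and weekends". The Data management section refers to sedentary time, light activity and MVPA during waking hours.

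**The concern.** Sedentary time is primary in four places and absent from the sample size calculation. A reader of the sample size section expects one test to decide the trial. A reader of the other sections expects two, and cannot tell whether one positive result is enough or both are needed. These are different trials, with different error rates and different power.

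The analysis section does not settle the matter, because its outcome is simply physical activity, and the measures section shows that this could be expressed in more than one way. If the text stays as it is, which result counts as the primary one could be settled after the data are seen. Schools are allocated by their own preference and not at random, so a primary outcome fixed in advance is one of the few safeguards available.

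**Working it through.** **Inputs**, all from the sample size section: f² = 0.15; alpha 0.05; power 0.80; one predictor (group); design effect 1.82 (coefficient of variation 0.15, five students per class, ICC 0.20); attrition 25%.

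**1. Reproduce the plan's figure.** Use the F test for one predictor, with non-centrality λ = f² × N and degrees of freedom 1 and N − 2.
- The smallest N with power of at least 0.80 is 55: λ = 0.15 × 55 = 8.25, df 1 and 53, power 0.805. A one-sided version would need only 43, so 55 is the two-sided figure.
- Design effect: 1 + ((0.15² + 1) × 5 − 1) × 0.20 = 1.8225.
- 55 × 1.82 = 100.1, taken as 100; 100 / 0.75 = 133.3, rounded up to 134.

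The figure reproduces. It covers exactly one test at 5%.

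**2. Two primary outcomes, success on either.**
- Two independent tests at 5%: family-wise error = 1 − 0.95² = 0.0975. For two-sided tests on jointly normal statistics, correlation only lowers this, so the range is 5% to 9.75%.
- Bonferroni: alpha per test = 0.05 / 2 = 0.025. At N = 55 (λ = 8.25, df 1 and 53), power is 0.713 per test.
- To restore 80% per test at 0.025, N = 66 (λ = 0.15 × 66 = 9.9). Then 66 × 1.82 = 120.12. Rounded up to 121, this gives 121 / 0.75 = 161.3, so 162 students. Rounded down to 120, as the plan rounds 100.1 to 100, it gives 120 / 0.75 = 160. Either way this compares with 134 planned.

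**3. Two primary outcomes, both must succeed.**
- Each test stays at 0.05, with no inflation of error.
- Joint power under independence = 0.805 × 0.805 = 0.648, about 65%. With positive dependence between the two tests it rises, at most to the single-test 0.805.

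**4. MVPA alone primary.** Alpha 0.05, power 0.805, N = 134, as stated.

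**Assumption in steps 2 and 3.** The article gives no effect size for sedentary time, so I used the same f² = 0.15 for it. A smaller effect would lower the power for sedentary time, and the joint power, below these figures. The calculations otherwise take the plan's own method, design effect and attrition as given.

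**The case against.** The best defence is that the sample size section does name a variable with a unit and ties 5% and 80% to it, that the arithmetic is right, and that the aim of increasing physical activity fits that choice. This stands. A reader might infer that the stated alpha and power attach to no defined test; that goes too far, because a powered outcome is named. The fault is that other sections contradict it.

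A reader might also infer that every intensity in every time window is a primary test with its own model. Five intensities by five windows would be 25 tests, with a family-wise error near 72% under independence. The documents do not support this. The measures section lists these as quantities to be derived and does not call each one primary, and the Data analysis section assigns separate models to five outcome domains, not to each cell. Independence is also impossible by construction: MVPA contains moderate and vigorous activity, and recess and lunch fall within the school day. Only the two-outcome count has a basis in the text.

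It is also fair that the Data management section, with its waking hours, together with the min/day unit, points towards a daily waking measure, and that averaging and valid-day rules commonly sit in a fuller document. That narrows the gap without closing it: the set of days remains open, and a fuller document should not have to choose between two conflicting published statements of what is primary.

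Finally, a reader might conclude that the sample size used the wrong alpha. That follows only if success on either outcome suffices. If both are required, 0.05 per test is correct and the shortfall is in joint power.

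**Conclusion.** The inconsistency is real and affects what the trial's primary conclusion will be. The stated 5% and 80% hold only if MVPA (min/day) is the sole primary outcome.

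- **Either outcome suffices:** family-wise error up to 9.75% without adjustment, or about 71% power per test at 0.025.
- **Both required:** error controlled at 5%, joint power about 65% under independence and higher if the outcomes are correlated.

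These figures assume f² = 0.15 for both outcomes and 55 effective observations. The 134 itself is correctly computed for one test.

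**What to change.** **Preferred.** In the abstract, the Effectiveness trial part of Procedures and participants, Table 2, the student measures section and the Data analysis section, name MVPA in min/day, over waking hours and averaged over one stated set of days, as the sole primary outcome, to match the sample size section. List sedentary time as key secondary, and the other intensities and time windows as secondary or exploratory. The Data analysis section must be included, or the analysed outcome will still be an undefined physical activity measure. The cost is wording and the loss of primary status for sedentary time; N stays at 134.

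**Alternative.** Keep both as primary and state whether either or both must succeed. In the either case, use Holm or Bonferroni and restate power as about 71% per test at 0.025, or recruit about 160 to 162 students to hold 80%. In the both case, keep 0.05 per test and state joint power as about 65% under independence, or a higher figure under a stated and justified correlation. The cost is lower stated power or a larger sample.

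The choice should be fixed before outcome data are examined.

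### The effectiveness sample size attaches two loss rates (30% and 25%) to the same 134 students, and Table 1 gives about 125; by the plan's own rule only 134 with 25% loss leaves the 100 analysable students required

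*Protocol article*

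**What the plan says.** All the figures are in the protocol article.

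- **Sample size and power calculation, Effectiveness trial, first paragraph.** The target is set for accelerometer-measured MVPA: "we are aiming to recruit a total of 134 students (intervention n=67; control n=67". The paragraph states that power remains sufficient after this loss: "Allowing for a 30% drop-out and incomplete data". The loss explicitly includes too little accelerometer wear.
- **Same section, second paragraph.** The inputs are "Assuming a moderate effect size (f² = 0.15), an α error probability=0.05, and power (1 – β error probability) = 0.80". With "the group variable as predictor, fixed effects were estimated to require 55 observations", a design effect of 1.82 raises the requirement to 100. The final step is "Accounting for 25% attrition, the final total sample size needed for the effectiveness trial is 134 participants", which is then divided by five students per class to give 27 classrooms.
- **Table 1, effectiveness trial, students row.** The entry reads "Around 125 students with disabilities, both males and females, aged 6–18 years".

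The article explains neither the difference between 30% and 25% nor that between 134 and 125.

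**The concern.** One recruitment number cannot be the result of a 25% allowance and also satisfy the same 100-student requirement after a 30% loss. The student number in Table 1 is lower still and meets the requirement at neither rate. A reader cannot tell which number and which rate govern the trial. The point concerns the sample size for the primary outcome. The larger rate is the one that names incomplete accelerometer data, so it is the more relevant to that outcome. The claim of sufficient power after 30% loss does not follow from the calculation printed beneath it.

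**Working it through.** **Inputs, all from the sample-size section except the last:** f² = 0.15, α = 0.05, power 0.80, one predictor (group); CV of class size 0.15, five students per class, ICC 0.20; loss of 25% or 30%; recruitment of 134, or about 125 (Table 1).

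**1. Reproducing the plan's own figure**

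- Unclustered sample: F test with 1 and N − 2 degrees of freedom and noncentrality f²N. N = 54 gives power 0.798 and N = 55 gives 0.805, so 55 is confirmed.
- Design effect: 1 + ((1 + CV²)m − 1) × ICC = 1 + (1.0225 × 5 − 1) × 0.20 = 1.8225, stated as 1.82.
- Analysable students: 55 × 1.82 = 100.1, stated as 100.
- Recruitment: 100 ÷ (1 − 0.25) = 133.3, rounded up to 134.

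The derivation is sound, and it rests on 25%.

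**2. The same rule at 30%**

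100 ÷ (1 − 0.30) = 142.9, so 143 students, or 29 classes of five (143 ÷ 5 = 28.6).

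**3. The four combinations, design effect held at 1.82 as in the plan**

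Analysed = recruited × (1 − loss). Effective n = analysed ÷ 1.82.

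| Recruited | Loss | Analysed | Effective n | Power |
|---|---|---|---|---|
| 134 | 25% | 100.5 | 55.2 | 0.81 |
| 134 | 30% | 93.8 | 51.5 | 0.78 |
| 125 | 25% | 93.75 | 51.5 | 0.78 |
| 125 | 30% | 87.5 | 48.1 | 0.75 |

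Only the first row reaches 100. The largest loss that still leaves 100 is 1 − 100/134 = 25.4% from 134 and 1 − 100/125 = 20.0% from 125.

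**4. Design effect recomputed on the class size left after loss**

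The plan divides 134 by five to get 27 classrooms, so five is the recruited class size. After loss, m = 5 × 0.75 = 3.75 or 5 × 0.70 = 3.5. With the same formula, ICC and CV:

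- m = 3.75: 1 + (1.0225 × 3.75 − 1) × 0.20 = 1.567
- m = 3.5: 1 + (1.0225 × 3.5 − 1) × 0.20 = 1.516

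| Recruited | Loss | Effective n | Power |
|---|---|---|---|
| 134 | 25% | 100.5 ÷ 1.567 = 64.1 | 0.86 |
| 134 | 30% | 93.8 ÷ 1.516 = 61.9 | 0.85 |
| 125 | 25% | 93.75 ÷ 1.567 = 59.8 | 0.84 |
| 125 | 30% | 87.5 ÷ 1.516 = 57.7 | 0.82 |

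All four exceed the 55 required. Uneven loss could make class sizes more variable. If the CV rose to 0.40 (an assumption; the article gives no such figure), the worst case, 125 at 30%, would have a design effect of 1 + (1.16 × 3.5 − 1) × 0.20 = 1.612, an effective n of 54.3 and power of 0.80.

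**The case against.** The strongest reply is that the shortfall comes from holding the design effect at five students per class after students have been lost. Losing students within classes also shrinks the clusters. On the recomputed design effect every combination exceeds 80%, so the statement that 134 students suffice after 30% loss can be defended within the classroom-level model. This stands as a point about power. It does not remove the conflict: the article does not make this argument, it inflates from a design effect fixed at five per class, and two loss rates and two student numbers remain in the text.

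The word "Around 125 students with disabilities, both males and females" opens with marks the Table 1 figure as approximate, and the sample-size section states 134 explicitly as its aim. That softens the second mismatch. Still, 125 is 6.7% below 134 (9 ÷ 134) and leaves 100 only if loss is at most 20%, below either stated rate.

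Two stronger readings are tempting but unsupported.

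- A reader might set the 27 classrooms against the staff entry in Table 1, "Teachers and teacher aides delivering the programme (approx. n=20", and infer fewer, larger classes and a larger design effect. The entry counts teachers and aides together, so it is not a count of classrooms. It may also cover the intervention schools only, since those are the schools delivering the programme during the comparison. About half of 27 classrooms, 13 or 14, is compatible with some 20 staff.
- A reader might infer that recruitment will stop at 125 because Table 1 says so. The article does not say that recruitment works from that table, which lists eligibility criteria.

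**Conclusion.** The point holds as an inconsistency in the stated figures, of modest severity. The 134 follows from 25% loss and not from 30%, and Table 1 gives a different number of students. With the design effect fixed at 1.82, three of the four combinations miss the plan's requirement by about 6 to 12 students, and power is 75% to 78% in place of 80%. With the design effect recomputed after loss, the same three have about 82% to 85%.

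A reader might conclude that the analysed sample must fall short, or that the trial is underpowered. Neither follows: 134 with 25% loss leaves 100.5, and the power deficit elsewhere depends on how the design effect is treated. These figures take the plan's effect size, ICC, CV and classroom-level clustering as given and say nothing about other levels of clustering.

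**What to change.** State one recruitment number and one loss rate in both the sample-size section and Table 1, and say that the rate covers drop-out and incomplete accelerometer data together. There are two ways to do this:

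- **Keep 134 with 25%.** Change the 30% sentence to 25% and the Table 1 entry to 134. The derivation, the 100 analysable students and the 80% power then stand as printed.
- **Keep 30% with 134.** Change Table 1 to 134, give the analysable number as about 94, and restate the power. Say whether the design effect is held at five students per class (about 78%) or recomputed on the class size after loss (about 85%).

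Either choice costs a sentence or two and one table entry. Neither changes the design, the analysis or the recruitment aim of 134. Under the second, the stated power moves away from 80%, in a direction that depends on the convention chosen.
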